# A randomized, controlled, multicenter clinical study of the “improved sitting Wuqinxi” intervention for mechanically ventilated patients in the intensive care unit

**DOI:** 10.1097/MD.0000000000023898

**Published:** 2021-01-29

**Keywords:** clinical study, ICU, improved sitting Wuqinxi, mechanical ventilation, randomized controlled

## Abstract

Supplemental Digital Content is available in the text

## Introduction

1

With the continuous progress of the theory and technology of mechanical ventilation, its application in the intensive care unit (ICU) has become increasingly common. Patients who need long-term mechanical ventilation in the ICU account for 4% to 13% of the total number of patients.^[1,2]^ Mechanical ventilation has become a powerful tool for the treatment of acute or chronic respiratory failure and other diseases. Thus far, studies on mechanically ventilated patients have mainly focused on in-hospital mortality and short-term physiological endpoints.^[3,4]^ However, surviving critically ill patients often develop persistent long-term physiological and psychological complications.^[5]^

Ventilator dependence is a common phenomenon in mechanically ventilated ICU patients. Previous studies have shown that 39% mechanically ventilated patients have difficulty weaning from mechanical ventilation and that 18% patients have prolonged mechanical ventilation time.^[6]^ Long-term mechanical ventilation leads to various complications, such as ICU-acquired weakness (ICU-AW), dysfunction of the cardiac circulation system, metabolic disorders, and psychological disorders. ICU-AW is a common complication in mechanically ventilated patients. The incidence of ICU-AW can reach up to 33.0% to 82.0% in patients on mechanical ventilation for >4–7 days.^[7,8]^ Complications caused by mechanical ventilation not only prolong the duration of mechanical ventilation and length of ICU stay but also seriously damage patients’ functional recovery.^[9,10]^

Wuqinxi is a traditional Chinese sports healthcare method created by Hua Tuo, an ancient famous doctor. Wuqinxi is based on the theories of yin and yang, 5 elements, Zang Xiang, and meridians. Five birds (deer, ape, bear, bird, and tiger) belong to the 5 elements (wood, fire, soil, gold, and water), which also correspond to the 5 Zang organs (the liver, heart, spleen, lung, and kidney). Wuqinxi has recognized clear disease prevention and health care effects and can regulate the 5 Zang organs.^[11]^

Long-term bed rest and immobilization lead to serious complications in critically ill patients on mechanical ventilation. Early activity is a very safe and effective strategy for disease prevention and rehabilitation.^[12–14]^ Previous studies have shown the safety and feasibility of early activity in mechanically ventilated ICU patients.^[15–17]^ However, the current unified early activity plan is relatively simple and its clinical efficacy is unclear. The traditional sitting Baduanjin intervention can achieve good clinical effects in patients with sepsis-induced mechanical ventilation.^[18]^ Based on this finding and the clinical characteristics of ICU patients, the traditional sports health care skill Wuqinxi was adapted into the “improved sitting Wuqinxi” intervention for severe patients under the guidance of professional Wuqinxi practitioners. Wuqinxi can reduce the incidence of delirium in mechanically ventilated ICU patients, shorten the duration of mechanical ventilation, and prevent complications and damages secondarily to mechanical ventilation. However, sufficient clinical evidence is needed to confirm its effectiveness. Therefore, our goal of this study will be to evaluatethe efficacy and safety of the improved sitting Wuqinxi intervention in mechanically ventilated ICU patients using a prospective, randomized, controlled, and multicenter clinical study design.

## Method and design

2

### Design

2.1

The study will be designed as a prospective, multicenter, single-blinded, randomized, controlled clinical trial. Three medical institutions in China will be involved in the study—Affiliated Hospital of Chengdu University of Traditional Chinese Medicine (TCM), Affiliated Hospital of Chengdu University, and Leshan Hospital of TCM. The study has been registered with the China Clinical Trial Registration Center (No. ChiCTR2000033391, submitted on June 1, 2020, Version. V1.0). After obtaining written informed consent, 160 patients will be randomly divided into the experimental and control groups in a 1: 1 ratio. Both groups will be given standardized comprehensive treatment (including mechanical ventilation) and routine care in the ICU. The management of the experimental group will also include Wuqinxi in addition to the standardized treatment. The purpose of this study will be to assess the effect of the improved sitting Wuqinxi intervention in mechanically ventilated ICU patients. The impact of clinical outcomes will be reported in accordance with the statement of 2013 Standard Protocol Items: Recommendations for Interventional Trials (refer to Document 1 [http://links.lww.com/MD/D659] for the Standard Protocol Items: Recommendations for Interventional Trials list).^[19]^ The research flowchart is shown in Figure 1. The timing of the study and the baseline data collection plan are shown in Figure 2.

**Figure 1 F1:**
[figure not shown]
Flow chart of the study design. ICU = Intensive care unit.

**Figure 2 F2:**
[figure not shown]
Schedule of enrollment, interventions, assessments, and data collection. Liver function index monitoring includes: ALT, AST, Tbil, ALP, GGT; Renal function index monitoring includes: BUN, Scr. ALP = Alkaline phosphatase, ALT = Alanine aminotransferase, AST = Aspartate aminotransferase, BUN = Blood urea nitrogen, ECG = electrocardiogram, GGT = γ-glutamyl-transferase, ICU = Intensive care unit, Scr = serum creatinine, Tbil = Total bilirubin.

### Moral certification

2.2

This study will be conducted in accordance with the Declaration of Helsinki (Edinburgh, 2000). The final revised draft (June 7, 2020 V1.0) and informed consent have been reviewed and approved by the Sichuan Regional Ethics Review Committee of The TCM/Medical Ethics Committee of The Affiliated Hospital of Chengdu University of TCM (No. 2019KL-031). All participants will also consent to the Standard Operation Training Procedure. If any amendments are made to the agreement, it will be reviewed and approved by the ethics committee again.

### Recruitment

2.3

The patients will be recruited from Affiliated Hospital of Chengdu University of TCM, Affiliated Hospital of Chengdu University, and Leshan Hospital of TCM. Before the initiating the study, written informed consent signed by the participants or their immediate family members will be obtained to ensure that they understand the relevant information regarding the clinical study, including the research purpose, intervention measures, intervention time, and possible risks and benefits.

### Sample size

2.4

According to the preliminary clinical research data, the total effective rate of “improved sitting Wuqinxi” in preventing and treating common complications and adverse outcomes in mechanically ventilated patients was statistically different between the groups. The test level was α = 0.05. The test efficiency was 1 - β = 0.80. The sample size was estimated using G∗Power (version 3.1.2, Franz faul, Universitat kiwl, Germany), and the effect size was set as d = 0.50. After calculation, the number of participants needed in each group was 64, totaling to 128 participants. Considering an attrition rate of ≤20%, the total number of participants required for this study was calculated to be 160, with 80 participants in each group.

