### Rejection, termination, and shedding criteria

2.8

All participants will be informed that they have the right to withdraw from the trial at any time and that they will receive standardized western medicine comprehensive treatment and ICU routine care regardless of participation. The reason for withdrawal will be recorded in their case report form (CRF).

All patients who do not meet the inclusion criteria will be excluded.

Patients who receive treatment but not in accordance to the regulations or those who have incomplete data will be excluded.

During the course of treatment, patients who withdraw voluntarily and those who experience adverse events (AEs) or serious AEs and not suitable for further treatment will be regarded as part of the attrition.

Patients with adverse reactions will be included in the statistics of adverse reactions. Patients who withdraw from more than 1/2 courses of treatment due to ineffectiveness will be included in the efficacy analysis.

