### Statistical analysis

3.7

Before analysis, the data of 2 participants with complete data will be carefully checked to ensure the accuracy of the data. All data will be analyzed by intention. SPSS version 22.0 (Chicago, IL) will be used to analyze the data. The measurement data will be represented as mean ± standard deviation. The paired t-test will be used to perform the before and after analyses of the same group. The chi-square test will be used for the counting data and the rank sum test will be used for grade data. The Kaplan–Meier method will be used for univariate analysis to explore each possible related factor. The multivariate Cox model will be used to adjust for variables with statistical significance (*P* < .05) in univariate analysis to detect the influence of these variables on the study measure outcomes.

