### Informed consent

3.8

We will provide each patient with a printed copy of the informed consent before initiating the trial, which will include the research name, research background, research methods, information on what the participants should do during the trial, inclusion/exclusion criteria, treatment plan and obligations, and possible adverse reactions caused by the intervention measures. We will make every effort to protect the privacy of patients’ personal medical data. Patients who voluntarily agree to participate in this study and those who will withdraw due to whatever reasons will continue to receive standardized western medicine comprehensive treatment and routine care in the ICU. Once the patients or their families sign the informed consent, their personal information and medical information will be officially used in this study.

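### The attrition allowance in section 2.4 assumes that dropouts leave the analysis, which fits the exclusion rules but not the analysis by intention, where power could be as low as about 71%

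*Protocol article*

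**What the plan says.** Section 2.4 (Sample size) gives the design inputs: "The test level was α = 0.05", "The test efficiency was 1 - β = 0.80" and "the effect size was set as d = 0.50". From these, "the number of participants needed in each group was 64, totaling to 128 participants". The last step is the attrition allowance: "Considering an attrition rate of ≤20%, the total number of participants required for this study was calculated to be 160, with 80 participants in each" arm.

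Four other places decide what attrition does to the analysis:

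- **Section 3.7 (Statistical analysis):** "All data will be analyzed by intention".
- **Section 2.8 (Rejection, termination, and shedding criteria):** patients who stop count towards attrition: "patients who withdraw voluntarily and those who experience adverse events (AEs) or serious AEs and not suitable for further treatment will be regarded as part". The same section excludes patients treated off-protocol or with incomplete data. It keeps in the efficacy analysis certain patients who withdraw for lack of effect, by a rule tied to half the course.
- **Section 3.4 (Compliance):** poor compliers are excluded.
- **Section 3.8 (Informed consent):** "those who will withdraw due to whatever reasons will continue to receive standardized western medicine comprehensive treatment and routine care in the ICU". Section 3.1.1 describes the control regimen in essentially the same terms.

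**The concern.** Dividing by 0.80 is the right correction when dropouts contribute no data: the sample shrinks and the effect in those who remain is unchanged. Under an analysis by intention, a patient who stops the exercise but has an outcome is still analysed in the experimental arm. The sample does not shrink. Instead, the arm difference may be diluted, because that patient's later care is that of the control arm. Dividing by 0.80 is not designed to offset dilution.

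Sections 2.4 and 3.7 therefore rest on different ideas of what happens to the 20%. If 3.7 governs, the 80% in 2.4 is not the power of the analysis by intention. The true figure could be higher or lower, depending on how many stop and what d stands for. At the unfavourable end, a null result would be read as coming from a trial with a 20% chance of missing the assumed effect, when that chance is about 29%.

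**Working it through.** **Inputs from the article.** α = 0.05, power 0.80, d = 0.50, 64 per group before attrition, attrition of at most 20%, 80 per group after it (all 2.4); 1:1 allocation (2.1). Sidedness is not stated. A two-sided test reproduces the printed number, while a one-sided test would need only about 50 to 51 per group.

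**Inputs assumed, because the article does not give them.** f = share of the experimental arm that stops Wuqinxi; r = share of the effect that stoppers keep; whether d = 0.50 is an as-randomised or a full-adherence effect.

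**Step 1: reproduce the plan.** A two-sample, two-sided t-test with d = 0.50 and 80% power needs n = 63.8, rounded up to 64 per group (128 in total). Then 128/(1 − 0.20) = 160, or 80 per group. Both printed figures reproduce. Power at 64 per group with d = 0.50 (noncentrality 0.50 × √(64/2) = 2.83) is 80.1%.

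**Step 2: removal reading (2.8 and 3.4 govern).** 80 × 0.80 = 64 per group with undiluted d = 0.50, so power is 80.1%. The allowance works.

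**Step 3: by-intention reading (3.7 governs), all 80 per group analysed.** If 0.50 is already an as-randomised difference, noncentrality is 0.50 × √(80/2) = 3.16 and power is 88.2%.

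If 0.50 is a full-adherence effect, the arm difference becomes

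d* = 0.50 × [1 − f × (1 − r)]

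| Stopping (f) | Effect kept (r) | d* | Power, 80 per group |
|---|---|---|---|
| 0% | – | 0.500 | 88.2% |
| 5% | 0 | 0.475 | 84.8% |
| 10% | 0 | 0.450 | 80.8% |
| 15% | 0 | 0.425 | 76.2% |
| 20% | 0 | 0.400 | 71.0% |
| 20% | 25% | 0.425 | 76.2% |
| 20% | 50% | 0.450 | 80.8% |
| 20% | 75% | 0.475 | 84.8% |

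Allowing for the extra variance from mixing stoppers and completers lowers the 71.0% slightly, to 70.2%.

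**Step 4: mixed case.** Suppose attrition is 20% in each group, part of it has no outcome, and the rest is analysed, with experimental stoppers at zero effect. Power is 73.2%, 75.5% and 77.8% when 25%, 50% and 75% of the attrition has no outcome.

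**Step 5: what 80 per group delivers.** The difference detectable with 80% power is d = 0.446, about 0.45. If 20% stop with no benefit, this corresponds to a full-treatment effect of 0.446/0.80 = 0.557, about 0.56. Restoring 80% power at d* = 0.40 would take 100 per group, before any allowance for missing outcomes.

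**The case against.** A reader might infer that the trial's power simply falls to about 71%. The documents do not support that. The figure needs four things at once: the full 20% stopping in the experimental arm, although the article gives 20% only as an upper limit; no benefit kept from sessions already done; an outcome recorded for every stopper; and d = 0.50 meaning a full-adherence effect. The article states none of the last three. Other equally admissible assumptions give 81% or 88%.

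The exclusion rules in 2.8 and 3.4 also cut against the dilution argument. If they govern, many stoppers are removed and the 80% arithmetic stands. The special rule that keeps certain withdrawals in the efficacy analysis suggests that other withdrawals are not kept. Section 2.8 calls the treatment-stoppers part of the attrition, so patients without usable data may make up the rest. Section 3.8 promises continued care after withdrawal, not continued outcome recording. Finally, 3.7 names no between-group t-test, so every power figure here is on the basis used for sizing in 2.4, not for a test listed in 3.7.

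All of this stands, and it limits the size of the point. It does not remove the mismatch: if patients are excluded as in 2.8 and 3.4, the analysis is not by intention; if it is by intention, a removal-type allowance does not describe what attrition does. Nor is this a detail left to an analysis plan, since 2.4 prints the number and 3.7 prints the principle.

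**Conclusion.** The point holds as an inconsistency between the attrition step and the stated analysis, not as an arithmetic error: 64, 128 and 160 all reproduce. The allowance agrees with the exclusion rules and disagrees with the analysis by intention.

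Under a true analysis by intention with 80 per group, power for the plan's d = 0.50 lies between about 71% and 88% for stopping of 0 to 20%, on both sides of the stated 80%. It drops below 80% only when stopping goes beyond roughly 10% with no effect kept, or when 20% stop and keep less than about half. The 71% is the least favourable end of that range and should be reported as such. Everything rests on the two-sided t-test basis of 2.4 and on assumptions about d and the effect kept. The point merits correction because the wording is easy to fix before results are known.

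**What to change.** Keep 160 patients and make three changes.

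1. Reconcile 2.4, 2.8, 3.4 and 3.7 so that all randomised patients are analysed as allocated. Withdrawal, off-protocol treatment and poor compliance should be recorded and reported, but should not remove a patient from that analysis.
2. Restate the end of 2.4, for example: *80 per group gives 80% power for an intention-to-treat difference of d of about 0.45; if 20% of the experimental group stop without benefit, this corresponds to a full-treatment effect of about 0.56, and power for 0.50 would be about 71%.* Say also whether d = 0.50 is meant as an as-randomised or a full-adherence effect.
3. State that outcomes are recorded to the planned end point for patients who stop the intervention. Ventilation time, ICU stay and cost arise during the ICU stay, so stopping the exercise need not make them missing.

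The cost is wording plus continued data collection in the ICU, with no extra patients. The downside is a possibly less favourable stated power at the attrition limit.

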### Randomization and allocation concealment

2.5

Members of the Sichuan Traditional Chinese Medicine Evidence-Based Medicine center will use SAS 9.2 software (SAS, Cary, NC) to generate 160 random serial numbers. After screening and baseline evaluation, mechanically ventilated ICU patients will be randomly divided into the experimental and control groups in a 1:1 ratio. The group allocation number will be provided in a continuously numbered sealed envelope of carbon-free paper. The envelope will be kept by the research administrator, who will not be directly involved in the recruitment or follow-up of any participants, and their group allocation number will be disclosed later. The administrator will open the envelopes and provide participants with their group allocation number on the day of inclusion. The distribution of patients in each experimental center is shown in Table 1.

**Table 1 T1:** Distribution of patients in each trial center.

Number of each center	Name of each center	Experimental group (patients)	Control group (patients)
01	Affiliated Hospital of Chengdu University of traditional Chinese Medicine	40	40
02	Leshan Hospital of traditional Chinese Medicine	20	20
03	Affiliated Hospital of Chengdu University	20	20
Total		80	80

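### Table 1 balances the arms within each of three centres, but the text names no centre-specific lists and the planned tests carry no centre term, so some power may be lost

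*Protocol article*

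**What the plan says.** All references are to the protocol article.

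- **Design (2.1):** "Three medical institutions in China will be involved in the study".
- **Randomization and allocation concealment (2.5):** SAS is used "to generate 160 random serial numbers", and after screening "mechanically ventilated ICU patients will be randomly divided into the experimental and control groups in a 1:1 ratio". The text mentions no stratum, block or centre-specific list. The section ends: "The distribution of patients in each experimental center is shown in Table 1". Table 1 gives, experimental/control, 40/40 in centre 01, 20/20 in centre 02 and 20/20 in centre 03, which totals 80/80.
- **Statistical analysis (3.7):** "The chi-square test will be used for the counting data and the rank sum test will be used for grade data". Measurement data get a within-group paired t-test, and no between-group test is named for them. Kaplan–Meier screening of possible related factors then feeds a Cox model with the variables that reach P < .05. Centre is not named in any of these analyses.
- **Sample size (2.4):** "The test level was α = 0.05"; "The test efficiency was 1 - β = 0.80"; effect size d = 0.50; 64 per group, 128 in total, raised to 160 for attrition of up to 20%.

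**The concern.** Two things do not fit together. First, within section 2.5 the table shows exact balance by centre, while the text describes a procedure that would not by itself produce it. A reader cannot tell whether Table 1 records stratified randomisation or a recruitment target.

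Second, if randomisation is stratified by centre, the analysis does not follow the design. When arms are exactly balanced within centres, differences between centres cannot contribute to the difference between arms. An analysis without centre nevertheless leaves that variance in the error term. For a difference in means or proportions, the reported standard error then exceeds the true one, confidence intervals are wider than they need be, and the test rejects less often than its nominal level.

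What is at stake is some power in a trial planned at 80%. There is no bias and no inflated type I error.

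**Working it through.** **1. The plan's own figure.** Two-sample t-test, two-sided α = 0.05 (the protocol does not state sidedness; a one-sided test would need 51 per group), power 0.80, d = 0.50. The noncentral t gives n = 64 per group, power 0.801. Allowing for attrition, 128 / (1 − 0.20) = 160. The stated 64, 128 and 160 reproduce.

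**2. Would the described list give Table 1?** Suppose one unstratified list with exactly 80 in each arm, and centres enrolling 80, 40 and 40. The probability of the Table 1 split is

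C(80,40) × C(40,20)² / C(160,80) = 0.022.

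So Table 1 implies either centre-specific lists that the text leaves out, or counts that a single list would deliver about 2% of the time.

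**3. Cost of leaving centre out of a comparison of means.** Let R² be the share of within-arm outcome variance that lies between centres. The documents do not give it, so a range is assumed. The 64 evaluable patients per arm are taken to remain balanced within centre.

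- True SE = unadjusted SE × √(1 − R²), so the SE is overstated by the factor 1/√(1 − R²).
- Noncentrality at d = 0.50: 0.50 × √(64/2) = 2.828. Critical value with 126 df: 1.979.
- Unadjusted type I error ≈ 2 × P(Z > 1.979/√(1 − R²)).
- Unadjusted power ≈ P(Z > (1.979 − 2.828)/√(1 − R²)).
- Power with centre: noncentral t with 124 df and noncentrality 2.828/√(1 − R²).

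| Assumed R² | SE overstated by | Type I error, unadjusted | Power without centre | Power with centre |
|---|---|---|---|---|
| 0 | 0% | 4.8% | 80.2% | 80.1% |
| 0.05 | 2.6% | 4.2% | 80.8% | 82.1% |
| 0.10 | 5.4% | 3.7% | 81.5% | 84.1% |
| 0.20 | 11.8% | 2.7% | 82.9% | 88.1% |

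The 4.8% in the first row comes from the normal approximation and is not conservatism: with no centre effect, the t-test has its nominal 5%. A simulation of 20,000 trials with the full Table 1 numbers (80 per arm) gave unadjusted type I errors of 4.8%, 4.5%, 3.7% and 2.9% for the four rows, against 4.8% to 5.1% with centre included. With 80 per arm, the calculated power gain is 0.9, 1.7 and 3.2 points at R² = 0.05, 0.10 and 0.20.

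**4. Cost for a binary outcome.** Table 1 sizes, assumed risk difference 0.22, 40,000 simulated trials, chi-square against Cochran–Mantel–Haenszel by centre:

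| Assumed control rates by centre | Power, chi-square | Power, CMH |
|---|---|---|
| 0.5 / 0.5 / 0.5 | 81.6% | 81.6% |
| 0.5 / 0.4 / 0.6 | 81.8% | 82.8% |
| 0.3 / 0.5 / 0.8 | 86.0% | 90.4% |

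The pattern is the same: no gain when centres are alike, about one point for modest differences, and four to five points for large ones.

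**The case against.** The strongest reply is that this is brevity, not error. Section 2.5 never says the list is unstratified; 160 is also the total of three centre lists (80 + 40 + 40), and Table 1 stands in the same section. Block details and model terms are often left to a full protocol or analysis plan that is not shown. Part of this stands: the article does not establish that a single unstratified list is used, and the 2% figure shows only that text and table need reconciling. But section 3.7 does name its tests, and those tests take no account of the centres within which Table 1 allocates.

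Several stronger readings are tempting and not supported:

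- *Standard errors are too wide.* This needs both within-centre balance and centre differences. If Table 1 is only a recruitment target under simple randomisation, unadjusted standard errors are valid on average, although adjusting for centre would still gain precision. If centres do not differ, nothing is lost.
- *Weaning practice, discharge rules or cost clearly differ between the hospitals.* The article names the hospitals and says nothing about differences in practice, so this can only be an assumption.
- *The analysis ignores centre altogether.* The P < .05 screen could admit centre to the Cox model. That route is data-driven, and it does nothing for the chi-square and rank-sum tests.
- *The Cox standard error would narrow.* It would not. The gain from centre there is mainly a less attenuated hazard ratio.
- *Cost suffers most.* No between-group test is named for cost, so any affected standard error is implied, not stated.

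**Conclusion.** The point holds in conditional form. Table 1 sets exact 1:1 allocation in each centre, the text does not say how that is achieved, and no test has a planned centre term. If arms are balanced within centre and outcomes differ between centres, unadjusted tests of mean and risk differences are conservative and lose some power. At 64 evaluable per arm and d = 0.50, the loss is zero with no centre effect, 1.3 points at a 5% share of variance, 2.6 at 10% and 5.2 at 20%. These shares are assumptions; the documents give none.

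Severity is minor. The error runs in the conservative direction and does not threaten validity. The required sample size does not change, because the stated 64 per group assumes no centre effect.

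**What to change.** In section 2.5, state that randomisation is stratified by centre, with separate lists that match Table 1. If Table 1 is meant only as a recruitment target, say so.

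In section 3.7, include centre in every between-group comparison, whatever the univariate screen shows:

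- complications: Cochran–Mantel–Haenszel test by centre;
- graded data: a centre-stratified rank test;
- time outcomes: centre as a stratum in the Cox model;
- measurement data such as cost: a centre term in whatever between-group comparison is used.

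The cost is a few sentences, a small change to list generation if the lists are not already centre-specific, and two degrees of freedom. No additional patients or data are needed.
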